## Abstract

**Background:**

After initial treatment of differentiated thyroid carcinoma (DTC) patients are followed with thyroglobulin (Tg) measurements to detect recurrences. In case of elevated levels of Tg and negative neck ultrasonography, patients are treated 'blindly' with Iodine-131 (^131^I). However, in up to 50% of patients, the post-therapy scan reveals no ^131^I-targeting of tumor lesions. Such patients derive no benefit from the blind therapy but are exposed to its toxicity. Alternatively, iodine-124 (^124^I) Positron Emission Tomography/Computed Tomography (PET/CT) has become available to visualize DTC lesions and without toxicity. In addition to this, ^18^F-fluorodeoxyglucose (^18^F-FDG) PET/CT detects the recurrent DTC phenotype, which lost the capacity to accumulate iodine. Taken together, the combination of ^124^I and ^18^F-FDG PET/CT has potential to stratify patients for treatment with ^131^I.

**Methods/Design:**

In a multicenter prospective observational cohort study the hypothesis that the combination of ^124^I and ^18^F-FDG PET/CT can avoid futile ^131^I treatments in patients planned for ‘blind’ therapy with ^131^I, is tested.

One hundred patients planned for ^131^I undergo both ^124^I and ^18^F-FDG PET/CT after rhTSH stimulation. Independent of the outcome of the scans, all patients will subsequently receive, after thyroid hormone withdrawal, the ^131^I therapy. The post ^131^I therapeutic scintigraphy is compared with the outcome of the ^124^I and ^18^F-FDG PET/CT in order to evaluate the diagnostic value of the combined PET modalities.

This study primary aims to reduce the number of futile ^131^I therapies. Secondary aims are the nationwide introduction of ^124^I PET/CT by a quality assurance and quality control (QA/QC) program, to correlate imaging outcome with histopathological features, to compare ^124^I PET/CT after rhTSH and after withdrawal of thyroid hormone, and to compare ^124^I and ^131^I dosimetry.

**Discussion:**

This study aims to evaluate the potential value of the combination of ^124^I and ^18^F-FDG PET/CT in the prevention of futile ^131^I therapies in patients with biochemically suspected recurrence of DTC. To our best knowledge no studies addressed this in a prospective cohort of patients. This is of great clinical importance as a futile ^131^I is a costly treatment associated with morbidity and therefore should be restricted to those likely to benefit from this treatment.

**Trial registration:**

Clinicaltrials.gov identifier: NCT01641679

## Background

Differentiated thyroid cancer (DTC) is the most frequent endocrine tumor, with an annual incidence per 100.000 individuals of 1 – 3 in men and 2 – 4 in women [1]. In general, DTC has an excellent prognosis, and only 5 to 10% will die of their disease [2,3]. Prognosis is less favorable when the disease recurs after primary treatment. Local or regional recurrence occurs in 5 – 20% of patients [4]. Distant metastases develop in up to 10%, usually in the lungs and bones [5]. Recurrences are usually detected during the early years of follow-up, but may occur years later [6]. As in many diseases, early detection of recurrence improves outcome and survival, because limited disease load may allow surgical resection and/or effective treatment with radioactive iodine (^131^I). Follow-up is therefore necessary throughout the patients’ life. Therefore, even though DTC incidence is low, many patients are currently under surveillance for a possible recurrence (estimated 500.000 in the United States) [7,8].

The serum marker Thyroglobulin (Tg) plays a pivotal role in the follow-up of differentiated thyroid cancer. Serum Tg should be undetectable in DTC patients following effective thyroid remnant ablation with ^131^I, so that any detectable level reflects (neoplastic) thyroid tissue [9]. The level of serum Tg is related to the amount of neoplastic thyroid tissue; it has been estimated that 1 g of neoplastic thyroid tissue corresponds with a serum Tg of 1 ng/ml during thyroid hormone replacement therapy, and with 2 – 10 ng/ml following recombinant human thyroid hormone stimulating hormone (rhTSH) stimulation [10,11]. A serum Tg cut-off level ≥ 2 ng/ml following rhTSH is highly sensitive to identify patients in whom persistent tumor may be found with imaging techniques [12,13].

When recurrent DTC is suspected because of serum Tg above the cut-off level, several imaging tests may be performed to detect the exact sites of recurrence. The sodium/iodide symporter (NIS) mediates iodide uptake in the thyroid gland and thyroid cancer cells [14]. The ability of the thyroid to accumulate Iodide via NIS is the basis for scintigraphic thyroid imaging with radioiodine (using the gamma-emitting ^123^I) as well as for therapy using the beta-emitter ^131^I, which targets and destroys iodide-transporting benign and malignant thyroid cells. In thyroid cancer, the primary therapy is total thyroidectomy, which in practice is near-total to spare adjacent nerves and parathyroids. Postoperatively, ^131^I is used to ablate these postoperative thyroid remnants, and to detect (using post ^131^I whole body scintigraphy) and treat potential metastases [15-17]. With this approach, highly selective radiation doses can be achieved in tumor tissue, often much higher than with external radiotherapy.

Historically, the follow-up of patients with DTC included scintigraphy after a low activity of ^131^I if serum Tg was elevated, but this is no longer recommended because of poor sensitivity [18-23]. To date, whole body scintigraphy after ‘blind’ administration of high ‘therapeutic’ activity of ^131^I is performed in these patients, during withdrawal of thyroid hormone replacement to stimulate uptake of iodine in cells of thyroidal origin, both to diagnose and re-stage the potential recurrence and to initiate its treatment [18,24-28]. This strategy can be effective, but an estimated 38% - 50% of patients will have a negative post-therapeutic ^131^I whole body scan and/or no objective therapy effect [29,30]. Such patients will have received a total body irradiation of 450 millisievert (mSv) and may have suffered from side effects such as nausea, sialoadenitis, loss of taste, or reduced spermatogenesis. Furthermore, their risk of secondary malignancies has increased [31,32]. All induced by a treatment from which they derived no benefit. Also, the prolonged thyroid hormone withdrawal and subsequent hypothyroidism necessary for ^131^I therapy have major impact on quality of life, with a majority of patients suffering from significant changes in physical, psychological, and social well-being [33-37]. The high frequency of high activities ^131^I from which patients do not derive any benefit but are exposed to its toxicity and potential adverse oncological effects, has led to a search for new diagnostic tools to improve the selection of patients for such treatment.

Nowadays, ultrasound of the neck is applied to detect a local recurrence or regional lymph node metastases allowing direct biopsy to confirm the diagnosis. Nonetheless, ultrasound is limited to the neck only, and when negative in the presence of detectable Tg, whole body evaluation is required.

Recently, Iodine-124 (^124^I) has become available as a novel radionuclide for whole body Positron Emission Tomography/Computed Tomography (PET/CT) in the follow-up of DTC [38-41], with a promising diagnostic accuracy and a considerably lower radiation exposure than whole body scintigraphy after therapeutic activity of ^131^I [39]. Furthermore, recent experience has shown that ^124^I PET/CT images may be representative for the biodistribution and radiation dosimetry of subsequent therapy with ^131^I [42,43]. Thus, ^124^I PET/CT may allow for more accurate restaging of patients in a whole body procedure, perform dosimetry for subsequent ^131^I therapy and predict the outcome of the treatment. However, some recurrent DTC lesions do not accumulate iodine, which is correlated with tumor dedifferentiation and this implies a poor prognosis [5]. Patients suspected of non-iodine accumulating DTC, so far only evident after futile blind ^131^I therapy, require restaging before local or systemic therapy may be applied. Metabolic PET imaging with the glucose analogon ^18^F-fluorodeoxyglucose (^18^F-FDG), especially during (rh)TSH stimulation, has a high sensitivity to detect recurrent DTC in patients with detectable Tg and negative iodine scintigraphy [44]. It may correlate with a more aggressive tumor behavior and poor prognosis [45], and can help to select patients for other treatment modalities (surgery, external beam radiotherapy or multikinase inhibitors [46-48]). ^18^F-FDG PET/CT is currently applied only when prior treatment and imaging with therapeutic activity of ^131^I has proven to be ineffective [49]. The value of ^18^F-FDG PET/CT before ^131^I treatment has not been tested.

At the biological level, ^124^I and ^18^F-FDG uptake is related to expression of the sodium iodine symporter (NIS) [16], while ^18^F-FDG uptake is related to hexokinase-I (HKI) and Hypoxia-inducible factor 1-alpha (HIF-1α) activity [50,51]. The evaluation of the relation of ^124^I and ^18^F-FDG PET/CT imaging findings and histopathological parameters (such as thyroglobulin, TTF1, Ki-67 and Cytokeratine-19 staining) and response to ^131^I treatment will give more insight in the fundamental knowledge about DTC.

The present study aims to test the power of combined for detect and characterize DTC lesions in patients with suspected recurrence. Based on the characteristics of ^124^I and ^18^F-FDG PET/CT, it is reasonable to assume that a combined strategy of imaging and histopathological evaluation at the time of suspected recurrence will yield adequate information on the disease stage prior to treatment with ^131^I, regardless of tumor dedifferentiation, with a potential impact on clinical decision making. The combination of both entities has been suggested in proof of concept studies [52], illustrated in Figure 1, but needs proper testing, to increase fundamental knowledge about DTC and further improve treatment.

**Figure 1 F1:**
[figure not shown]
**Images from two different patients scanned with both **^**124**^**I and **^**18**^**F-FDG PET/CT.** The ^124^I PET/CT of patient 1 **(a)** shows multiple ^124^I negative pulmonary nodules, which are evidently ^18^F-FDG positive **(b)**. The thoracic wall lesion of patient 2 is clearly ^124^I avid **(c)** and showing no uptake on the ^18^F-FDG PET/CT **(d)**.

The multicenter design of this study requires highly standardized procedures for ^124^I PET/CT. Previously nationwide standardization was done for ^18^F-FDG PET/CT in the Netherlands, which eventually evolved into the European EARL accreditation system [53,54]. In order to compare the scans between centers calibration and standardization of the ^124^I PET/CT scans prior to the start of the study will be done a in quality assurance and quality control (QA/QC) program.

In summary, therapy with high activities of ^131^I for recurrent DTC is effective in many cases, but the current blind approach also leads to overtreatment, delay, and unnecessary decrease in quality of life in a significant number of cases. As we described, a combination of diagnostic tests has a potential to allow earlier and better restaging and selection for treatment. The proposed trial aims to test the value and optimal implementation of these new tests, standalone and in combination, to derive parameters for a new personalized strategy for diagnosis and treatment of patients with (suspected) recurrent DTC.

## Methods and design

### Study objectives

The primary aim of the study is to evaluate the value of combined imaging with ^124^I and ^18^F-FDG PET/CT in the prevention of futile treatment with high therapeutic activity of ^131^I. Interpretation of both PET-scans will lead to a positive or negative treatment proposal. This will be compared with the actual response on therapy. The definition of a futile treatment will be a negative post blind ^131^I therapy scintigraphy.

We define four secondary aims. Firstly, our aim is to organize a synchronized introduction and QA/QC of ^124^I PET/CT in the Netherlands. More specifically, we aimed to create a procedure for the cross-calibration of ^124^I PET/CT in a multicenter setting, which guarantees reliable and comparable quantification, and is practical to use. The procedure should result in calibration factors per scanner and an indication of a measurement threshold of the scanner, which is defined as the lowest activity that can be reliably quantified. The measurement threshold will be determined per vendor.

Secondly, translational correlation of ^124^I and ^18^F-FDG PET/CT with histopathology (where available) and treatment outcome will be done, in an explorative setting. The outcome of the treatment is defined as a positive or negative post-therapy scan. This scan and both ^124^I and ^18^F-FDG PET/CT will be correlated with histopathological features. The expression of different markers will be quantified in the samples. In this way we aim to determine which histopathological features of both primary tumor and metastatic lesions can predict outcome of the scans.

Thirdly, the study aims to investigate whether ^124^I PET/CT has the same diagnostic, dosimetric and prognostic yield during stimulation with rhTSH as with hormone withdrawal combined with low-iodine diet. Because ^124^I PET/CT will be performed both after stimulation with rhTSH and after withdrawal from levothyroxine it is possible to determine any differences in outcome from the two scan preparation strategies. Both visual assessment as the quantifiable data will be compared. As simultaneous administration of ^131^I and ^124^I is required this can only be done in selected.

Fourthly, we aim to compare ^124^I PET/CT and ^131^I scintigraphy dosimetry and correlate the results with clinical outcome. As ^124^I PET cannot be considered as the golden standard for dosimetry of iodine therapy the dosimetry based on ^124^I PET will be compared with ^131^I-scintigraphy dosimetry. An additional phantom study will be performed to correlate the results.

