#### Pre-therapy phase

Patients with biochemically confirmed recurrent DTC, will undergo ^18^F-FDG and ^124^I PET/CT imaging after pre-treatment with two injections of rhTSH. ^18^F-FDG will be administered and ^18^F-FDG PET/CT will be performed 60 minutes post injection. Subsequently, 74 megabecquerel (MBq) of ^124^I is administered intravenously. ^124^I PET/CT scans are then performed 24 and 96 hours after administration of ^124^I.

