#### Between ‘pre-therapy phase’ and ‘therapy phase’

If either the ^18^F-FDG PET/CT or the ^124^I PET/CT shows metastatic lesions and it is possible to acquire a biopsy from the lesion, this will be done to correlate histopathological characteristics with both the result of the scans and the resection specimen of the original tumor. If multiple metastatic lesions are present on either of the scans, a biopsy will be pursued to acquire from every lesion, but only if the ^124^I or FDG uptake differs between the different lesions. This will be done in easily accessible metastatic lesions without large risks of complications and/or discomfort for the subject.

After the pre-therapy phase, subjects will start thyroid hormone withdrawal 4 weeks prior to ^131^I therapy. A low-iodine diet (LID) will be prescribed one week before the therapy.

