#### Therapy phase

Subjects will undergo ^131^I therapy with 7400 MBq of ^131^I orally. In a subgroup of subjects (in selected centers) additional ^124^I PET/CT scans will be performed for dosimetric evaluation. Furthermore, the influence of the method of preparation for the scan, either withdrawal of thyroid hormone or rhTSH stimulation, will be evaluated. Seven days after administration of ^131^I a post-therapy scintigraphy is made, combined with SPECT/CT if available.

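### The third aim attributes differences between the two 124I scans to scan preparation, but preparation is fully aliased with scan order and with 131I co-administration

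*Protocol article*

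**What the plan says.** Under Study objectives, the third secondary aim asks whether 124I PET/CT "has the same diagnostic, dosimetric and prognostic yield during stimulation with rhTSH as with hormone withdrawal combined with low-iodine diet". The article then states what the design can deliver: since the scan is made under both preparations, "it is possible to determine any differences in outcome from the two scan preparation strategies". It adds a constraint in the same paragraph: "As simultaneous administration of ^131^I and ^124^I is required this can only be done in selected" (the sentence ends there in the article).

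The schedule is given under Study procedures:

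- Pre-therapy phase: patients "will undergo ^18^F-FDG and ^124^I PET/CT imaging after pre-treatment with two injections of rhTSH".
- Between the pre-therapy and therapy phases: biopsies may be taken from accessible lesions. "After the pre-therapy phase, subjects will start thyroid hormone withdrawal 4 weeks prior to ^131^I therapy", with the low-iodine diet in the last week.
- Therapy phase: "Subjects will undergo ^131^I therapy with 7400 MBq of ^131^I orally". Further 124I scans are made in a subgroup at selected centers, and the effect of the preparation method is to be evaluated there.

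Study endpoints lists this item more mildly, as a correlation between the findings under the two preparations.

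**The concern.** Study objectives and Therapy phase both present the comparison as one of preparation methods. The two scans also differ in two other respects, in the same way for every patient: one is earlier and the other later, and one is made without therapeutic 131I and the other with it. The article treats the simultaneous administration as a limit on where the scans can be done. It does not treat it as something that affects how the comparison is read.

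At stake is the meaning of the result. A difference between the scans could be credited to preparation when it comes from order, elapsed time or 131I. Similar findings could likewise arise from effects that offset one another. Either reading could influence how patients are prepared for later 124I PET/CT.

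**Working it through.** **Plan's own figure.** The article gives no sample size or precision for the third aim. Its only such figure (Sample size calculation) concerns the primary aim: an exact 95% interval extending 10% from an expected 40% with 100 patients. It reproduces: 40/100 gives 30.3% to 50.3%, that is 9.7 points below and 10.3 above. It has no bearing on this point.

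**Inputs.** The two scans, as scheduled:

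| Scan | Preparation | Order | Therapeutic 131I on board | Source |
|---|---|---|---|---|
| Pre-therapy | rhTSH | first | no | Pre-therapy phase; 131I therapy less than 12 months before inclusion is an exclusion criterion |
| Therapy (subgroup) | withdrawal plus low-iodine diet | second | yes, simultaneous | Study objectives; the section between the two phases; Therapy phase |

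The low-iodine diet belongs to the declared contrast, so it is not counted as an extra confounder.

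**Model.** Write the expected outcome of a scan as

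E(Y) = m + a·W + b·S + g·C

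where W = 1 for withdrawal, S = 1 for the second scan, C = 1 if 131I is co-administered, and m is the patient's own level.

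- rhTSH scan: (W, S, C) = (0, 0, 0), so E(Y) = m.
- Withdrawal scan: (W, S, C) = (1, 1, 1), so E(Y) = m + a + b + g.
- Within-patient difference: a + b + g.

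**Can a be separated?** The design matrix has rows (1, 0, 0, 0) and (1, 1, 1, 1). Its rank is 2, for 4 parameters, and a is not estimable. More patients only repeat these two rows, so the rank stays at 2 at any sample size.

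**Which alias matters?** Setting g = 0, as if the effect of 131I on the scan were absent or perfectly corrected, leaves a + b, and a is still not estimable. It becomes estimable only when neither order nor 131I status is tied to preparation. That layout was checked only to settle the identification question and is not a proposed schedule.

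**Consequences.**

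- If a = 0, the observed difference is b + g, which need not be zero.
- If a = −(b + g), the observed difference is zero although preparation has an effect.

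**Do other data in the article help?** The repeat PET at six months follows the 131I therapy and is done only for a modality that was positive before therapy. It does not supply a withdrawal scan without 131I.

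**The case against.** The strongest reply is that the constraint is disclosed and the claim is modest. The paragraph that makes the claim also says that simultaneous 131I is required. Nowhere does the article say that differences come from preparation alone. The endpoint is labelled a correlation, and no equivalence margin or superiority test is planned. The order follows from the primary design, in which imaging precedes therapy. Interim biopsies are limited to easily accessible lesions, so they are a thin addition to the argument.

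Most of this stands, and it limits the point to interpretation. It does not answer the central statement: that differences due to the two preparations can be determined is a property the design lacks, and disclosing 131I does not supply it. An analysis plan that is not shown could not supply it either.

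Three stronger readings are tempting and are not supported:

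- *That the bias is large because 131I far exceeds 124I.* The ratio 7400/74 = 100 assumes that the second 124I activity equals the 74 MBq of the pre-therapy scan, which the article does not say. It is also a ratio of administered activities. Nothing in the document converts it into an effect on a 124I reading.
- *That the phantom work is deficient.* The article says only "An additional phantom study will be performed to correlate the results", under the fourth aim. Whether 131I is included is neither stated nor excluded, and such detail is commonly left to a full protocol. A phantom correction would in any case leave order and elapsed time aliased with preparation.
- *That the trial will report equivalence of the preparations.* The aim asks about the same yield, but this is a question; no such conclusion is planned in the text.

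**Conclusion.** The point holds as a fault in the stated aim. Preparation, scan order or elapsed time, and 131I co-administration occur in only two joint patterns, so the effect of preparation is not identifiable from these scans, whatever the number of patients.

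This rests on the sequence in the text: rhTSH first without therapeutic 131I, withdrawal second with it. Figure 2 is not shown, but its legend agrees with that sequence. The size and direction of any bias cannot be worked out from the document, so no claim is made that it is material.

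The importance is low. The aim is secondary and confined to a subgroup; the primary endpoint, the sample size and the stopping rule are unaffected.

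**What to change.** In Study objectives and in Therapy phase, restate the third aim as a descriptive within-patient comparison of the pre-therapy rhTSH 124I scan without 131I and the later 124I scan after withdrawal plus low-iodine diet with co-administered 131I. Align the endpoint label in Study endpoints for consistency; its present wording makes no causal claim. Add one sentence saying that the effects of preparation, order or elapsed time, and 131I cannot be separated, and that no conclusion of same yield or superiority will be drawn for a preparation method.

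The cost is a few lines of text and a narrower secondary conclusion. No study procedure changes.

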### Study design

This study is designed as a nationwide multicenter observational cohort study. The study population includes patients with biochemically suspicion (i.e. increase Tg levels) of recurrence of their previously completely removed thyroid carcinoma without evidence of local recurrence, planned for ‘blind’ therapeutic activity of ^131^I.

The patients to be included in the study should meet the following inclusion criteria:

1. Patients with a history of differentiated thyroid cancer

2. After complete thyroidectomy and ablation of functional remnants with ^131^I.

3. Planned for ‘blind’ treatment with high activity of ^131^I based on biochemically suspected recurrence, defined as a Tg-level above 2.0 ng/ml.

4. Ultrasonography of the neck performed < 2 months prior to inclusion.

If one of the following criteria is met patients will be excluded from the study:

1. Age < 18 years

2. Pregnancy

3. Incapacitated subjects

4. Contrast enhanced CT performed < 4 months prior to inclusion

5. ^131^I therapy performed < 12 months prior to inclusion

6. Indication for other therapy modality (i.e. surgery in case of a positive ultrasonography, radiotherapy, embolization or chemotherapy)

